### 2.7. Power Calculation and Statistical Analyses

In order to detect a clinically relevant difference of 2.5 mm Hg in the primary outcome measure of systolic home blood pressure with at least 90% power, a sample size of 31 volunteers is required. A reduction of 2.5 mm Hg in blood pressure translates to a risk reduction at a population level in stroke, hypertension and CVD of between 7% and 15% [133]. This calculation assumes a within-group standard deviation (SD) of 14 mmHg, a within-subject correlation between the 4 blood pressure measures at each visit of *r* = 0.6 based on previous studies [135,136], and a between-phase within-subject correlation of *ρ* = 0.5. This correlation (*ρ*) and the cross-over design reduces the number of required participants by a factor of (1 − *ρ*)/2 = 4 [153] i.e., from approximately *n* = 124 for a parallel group design using ANCOVA (*n* = 62 per group) to *n* = 31 subjects in total. To account for a withdrawal rate of 30%, an additional 9 volunteers will be recruited. 

To detect a statistically significant difference in *Z* scores for the cognitive outcomes Total Cognitive Functioning, Memory, Processing Speed and Executive Functioning, a sample size of *n* = 22 is required. This calculation assumes power equal to 0.8, an α level of 0.05, a correlation between measurements of 0.6, and a moderate effect size (Cohen’s *d* = 0.5) signifying a treatment effect of 0.5 SD [137]. A moderate effect size has been chosen on the basis of similar nutritional intervention studies that have detected significant improvements in cognitive outcomes, which may indicate restoration of cognitive function and reversal of cognitive decline [46,152].

Independent *t*-tests and chi-squared tests will be used to compare baseline demographic, cardiometabolic, cognitive, well-being and dietary characteristics between those who completed the study and those who withdrew.

To analyse the difference between dietary interventions a linear mixed-effects analysis will be performed to measure both within and between subject effects for cardiometabolic and cognitive outcomes. Potential confounding variables including weight loss, changes to physical activity, medications or dietary supplements, carryover and period effects will be included in the analysis. Potential carryover effects and treatment-period effects will be assessed by adding treatment × phase and treatment × order interaction terms in the mixed effects analyses. We will also assess possible seasonal effects by including a term for treatment × season interaction in a secondary analysis with season coded as a binary variable for Autumn or Spring versus Winter or Summer. Diet × period × energy intake interaction terms will be used to determine whether there are any significant changes in diet (total energy intake, macronutrient intakea, micronutrient intakes including sodium, and fatty acid ratios) between the two diet phases. If a significant change is detected in cognitive function a hierarchical regression will be performed to determine the influence of cardiometabolic outcomes. All statistical analyses will be conducted using SPSS for Windows, version 21.0 (SPSS Inc., Chicago, IL, USA) and Stata (version 14.2, StataCorp, College Station, TX, USA). Data will be presented as means ± standard deviation (SD) for descriptive statistics and as means ± standard error (SEM) for reporting estimated effects. All tests will be 2-tailed and *p*-values < 0.05 will be deemed statistically significant.

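### The primary sample size of 31 does not follow from its stated inputs: read directly, they require about 61 to 64 subjects, and 31 gives about 61% power rather than 90%

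*Protocol article*

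**What the plan says.** All of the primary calculation is in Section 2.7 of the protocol article.

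- Target (a difference of 2.5 mmHg, which the protocol regards as clinically relevant): "in the primary outcome measure of systolic home blood pressure with at least 90% power, a sample size of 31 volunteers is required".
- Variability: "This calculation assumes a within-group standard deviation (SD) of 14 mmHg".
- Repeated measures: "a within-subject correlation between the 4 blood pressure measures at each visit of *r* = 0.6".
- Crossover: "a between-phase within-subject correlation of *ρ* = 0.5".
- Reference design: about 124 in total "for a parallel group design using ANCOVA (*n* = 62 per group").
- Reduction: the correlation ρ and the crossover "reduces the number of required participants by a factor of" (1 − ρ)/2, which the text sets equal to 4. This takes 124 to 31 subjects in total.
- Nine more volunteers are added for a 30% withdrawal rate, giving the forty in the abstract.

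The end of Section 2.7 makes all tests two-tailed at 0.05. Section 2.5.1 describes the primary measurement: home blood pressure morning, afternoon and evening for six days at each of four time-points, with three readings on each occasion.

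**The concern.** Section 2.7 gives enough inputs to attempt the calculation, and the most direct attempt does not give 62 per group. It gives almost exactly twice that. If the parallel figure is half of what it should be, so is the crossover figure, and the stated power is well below 90%.

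This is the only justification of the trial's size for its primary outcome. The protocol calls 2.5 mmHg clinically relevant. A reader who trusts the 90% would take a non-significant result as good evidence against an effect of that size, and the inputs as written do not support that conclusion.

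**Working it through.** **Inputs.** From Section 2.7: difference δ = 2.5 mmHg, SD = 14 mmHg, 90% power, k = 4 measures per visit with within-visit r = 0.6, ρ = 0.5, two-sided α = 0.05. Not stated: the correlation r01 between a baseline and a follow-up measure. The main calculation assumes r01 = 0.6.

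**The protocol's own chain.** 124 / 4 = 31, and 31 + 9 = 40. The division is right. At ρ = 0.5, (1 − ρ)/2 = 0.25, so the printed value of 4 should be 1/4; the text nevertheless applies the reduction correctly. The problem lies in the starting figure of 124.

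**Parallel ANCOVA on means of k baseline and k follow-up measures.**

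- Variance of a mean of 4, in units of SD²: v = (1 + 3 × 0.6)/4 = 0.700.
- ANCOVA variance factor: f = v − r01²/v = 0.700 − 0.36/0.700 = 0.700 − 0.514 = 0.186.
- n per group = 2 × (1.960 + 1.282)² × 14²/2.5² × f = 659.0 × 0.1857 = 122.4, so 123 per group and about 245 in total.
- With 62 per group, the parallel design has 64% power (normal approximation).

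**Crossover.**

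- 245 × 0.25 = about 61 subjects (normal approximation).
- Cross-check: SD of the within-person difference = √(2 × 196 × 0.1857 × 0.5) = 6.03 mmHg. With the noncentral t on n − 2 degrees of freedom, 63 subjects give 89.9% and 64 give 90.4%.
- Power for 2.5 mmHg by t: 61% at 31 completers (64% by normal approximation), 56% at 28 (30% withdrawal from 40), 72% if all 40 complete.
- Difference detectable with 90% power at 31: about 3.6 mmHg by t (3.5 by normal approximation).

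**Sensitivity to the unstated r01** (k = 4, within-visit r = 0.6; n by normal approximation, power by t):

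| r01 | f | n per group, parallel | crossover n | power at 31 |
|---|---|---|---|---|
| 0.50 | 0.343 | 226 | 113 | 38% |
| 0.60 | 0.186 | 122 | 61 | 61% |
| 0.65 | 0.096 | 63.5 | 32 | 87% |

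**Sensitivity to the number of measures** (one common correlation of 0.6):

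| k before and after | crossover n | power at 31 |
|---|---|---|
| 4 | 61 | 61% |
| 6 | 42 | 77% |
| 9 | 28 | 91% |
| 18 | 14 | above 99% |

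**Other analyses of the stated inputs** (two-sided, 90% power; crossover totals): change score with 4 before and 4 after, 66; ANCOVA with 1 before and 4 after, 112; ANCOVA with 1 and 1, 211; mean of 4 without baseline, 231. Each needs more than 61.

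**The case against.** The strongest objection is that the main calculation supplies an input the protocol does not give. Section 2.7 places r = 0.6 among the measures at a visit and ρ = 0.5 between phases, and is silent on baseline to follow-up. With r01 near 0.65 the crossover needs about 32. This stands as a limit on how firmly any single replacement figure can be stated. It does not vindicate 31, because it requires measures taken weeks apart to correlate more strongly than measures within one visit.

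A second objection also stands in part. Four measures per visit is not the schedule in Section 2.5.1, which yields 3 × 6 = 18 sessions (54 readings) per time-point; the only four there is the number of time-points. More measures would raise the power, and nine or more would reach 90% at 31. However, those figures assume one correlation of 0.6 across all sessions, both within a week and across weeks, which is optimistic. They are also not the calculation that Section 2.7 reports.

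Three stronger readings are tempting, and the documents do not support them:

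- A reader might infer that the trial as designed has 61% power and would miss a true 2.5 mmHg effect about 39% of the time. That holds only for four measures and r01 = 0.6.
- A reader might infer that a factor of 2 was certainly dropped. The match of 123 per group to a stated total of about 124 suggests that a per-group number was taken as the total, but the working is not shown.
- A reader might infer that nothing could rescue 31. A higher r01 or more measures could, but neither is what Section 2.7 states.

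Reading 31 as a number per sequence does not help either: the text says it is the total, and 31 + 9 matches the forty recruited.

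**Conclusion.** The point holds as a calculation that cannot be reproduced from its own inputs. With r01 assumed to be 0.6, those inputs give about 123 per group rather than 62, and about 61 to 64 crossover subjects rather than 31; 31 completers then have about 61% power. Across r01 from 0.5 to 0.65 with four measures, power at 31 runs from about 38% to 87%, so it stays below 90% throughout. Reaching 31 takes either a baseline-to-follow-up correlation above the within-visit value or more measures than Section 2.7 states. The claim of at least 90% power is therefore unsupported as written. What the true power is under the Section 2.5.1 schedule cannot be settled from the document.

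**What to change.** Keep the recruitment target and revise the power paragraph in Section 2.7:

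1. Correct the printed factor from 4 to 1/4.
2. State the baseline-to-follow-up correlation and its basis.
3. Reconcile the four measures per visit with the home schedule in Section 2.5.1, saying what one measure is (a reading, a session or a daily mean) and how many enter the analysis.
4. Recompute the parallel and crossover figures from those inputs.
5. Replace the 90% claim with the resulting power and show the range. If the inputs stay as now written, that means about 123 per group (245 in total) for the parallel design, about 61 to 64 for the crossover, and about 61% power for 2.5 mmHg at 31 completers (90% for about 3.6 mmHg), labelled as conditional on r01 = 0.6 and four measures.
6. Note that on those inputs a non-significant result would not exclude a 2.5 mmHg difference.

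The cost is a rewritten paragraph and possibly a less favourable stated power. No participants, visits or procedures are added.

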### 2.5. Outcomes

#### 2.5.1. Blood Pressure

Home measured systolic blood pressure will be the primary outcome. Home blood pressure assessments have stronger predictive power for complications of hypertension and mortality than clinic blood pressure assessments [127,128]. Further, multiple home blood pressure measurements have comparable reliability to ambulatory blood pressure measurements in evaluating hypertension [129]. Participants will be provided with an A&D Company Ltd. digital blood pressure monitor (model UA-767) and instructed to measure their blood pressure and heart rate every morning, afternoon and evening, for a period of six days at each of the four study time-points. Participants will be asked to take measurements at consistent times each day, at least one hour after the consumption of caffeine or alcohol and 30 min after food or exercise. Each measurement of blood pressure will follow a five-minute resting period in the seated position and three readings will be taken, spaced at least one minute apart [130,131]. Home blood pressure will be recorded at four time-points over the course of the trial, one week prior to clinic assessment visits (at pre-baseline, Week 7, Week 15 and Week 23). Blood pressure will also be measured in-clinic using an Omron Healthcare Co. digital blood pressure monitor (model 1A1B Hem-7000-CIL) at the beginning and end of each dietary phase. A similar protocol for in-clinic measurements will be used, with blood pressure and heart rate measurements following a five-minute resting period in the seated position. Three readings will be taken at each visit, spaced at least one minute apart.

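### The primary-outcome sample size of 31 does not follow from its own inputs: the most favourable reading needs about 62 completers, and 31 give at most about 61% power for 2.5 mmHg

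*Protocol article*

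**What the plan says.** All the relevant figures are in section 2.7 of the protocol article.

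- Target: "In order to detect a clinically relevant difference of 2.5 mm Hg in the primary outcome measure of systolic home blood pressure", and the claim "with at least 90% power, a sample size of 31 volunteers is required".
- Variability: "This calculation assumes a within-group standard deviation (SD) of 14 mmHg".
- Repeated measures: "a within-subject correlation between the 4 blood pressure measures at each visit of *r* = 0.6".
- Crossover gain: "a between-phase within-subject correlation of *ρ* = 0.5".
- Parallel-group starting point: about 124 participants "for a parallel group design using ANCOVA (*n* = 62 per group". The article multiplies this by (1 − ρ)/2, which it writes as equal to 4, to reach 31.
- Test: two-tailed at 0.05, stated for all analyses at the end of the same section.

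Section 2.5.1 describes the measurements. Home pressure is taken "every morning, afternoon and evening, for a period of six days at each of the four study time-points", with three readings on each occasion. Clinic pressure is three readings per visit.

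**The concern.** The article gives its inputs, an intermediate figure and a result, so the calculation can be checked. An SD of 14 mmHg against a difference of 2.5 mmHg is a standardised effect of 2.5/14 = 0.18, for which 62 per group looks far too few even after generous allowance for repeated measures and baseline adjustment. The intermediate figure carries everything, because 31 is simply a quarter of 124.

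This is the only power statement for the primary outcome. If it is wrong, a reader of a non-significant result would credit the trial with a 90% chance of finding a difference that the protocol calls clinically relevant, and the stated assumptions do not support that.

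**Working it through.** **Inputs** (section 2.7): d = 2.5, SD = 14 (variance 196), four measures per visit, r = 0.6, ρ = 0.5, two-sided α = 0.05, power 0.90, so (1.960 + 1.282)² = 10.51.

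**1. The plan's last step.** (1 − 0.5)/2 = 0.25, and 124 × 0.25 = 31. This reproduces. The expression equals 0.25, not 4; the arithmetic performed is a division by 4, which is correct for ρ = 0.5. So this is a slip of notation and did not cause the error.

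**2. The parallel-group size.** n per group = 2 × 10.51 × 196 × f / 6.25 = 659 × f, where f is the variance factor from repeated measures and baseline adjustment. For ANCOVA with p baseline and q follow-up measures, all correlated r:

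f = (1 + (q − 1)r)/q − r² / [(1 + (p − 1)r)/p]

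| Reading | f | n per group (rounded up) |
|---|---|---|
| ANCOVA, 1 baseline, 4 follow-up | 0.70 − 0.36 = 0.34 | 225 |
| Change score, 4 and 4 | 0.70 + 0.70 − 1.20 = 0.20 | 132 |
| ANCOVA, 4 baseline, 4 follow-up | 0.70 − 0.36/0.70 = 0.186 | 123 |

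The stated figure is 62. Relaxing the test does not reach it either. For ANCOVA 4/4, a one-sided test with 90% power needs 100 per group, a two-sided test with 80% power needs 92, and a one-sided test with 80% power needs 73.

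**3. The crossover size.** For ANCOVA 4/4 the unrounded figure is 122.4 per group, so 244.8 in total. 244.8 × 0.25 = 61.2, or 62 completers.

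**4. Power with 31 completers.** The SD of the within-person diet difference is 14 × √f × √(2(1 − ρ)). With ρ = 0.5 the last factor is 1. Power is from the noncentral t for a paired comparison.

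| Reading | SD of difference | Power for 2.5 mmHg | Difference with 90% power |
|---|---|---|---|
| ANCOVA 4/4 | 14 × √0.186 = 6.0 | 61% | 3.6 mmHg |
| ANCOVA 1/4 | 14 × √0.34 = 8.2 | 38% | 4.9 mmHg |

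The normal approximation gives 64% in place of 61%.

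**5. What 31 would require.** For 90% power at 2.5 mmHg with 31 completers, the SD of the difference must be at most about 4.15 mmHg, against 6.0 on the best reading. Holding the other inputs, that means a between-phase correlation of about 1 − 4.15²/(2 × 196 × 0.186) = 0.76 under ANCOVA 4/4, and 0.87 under ANCOVA 1/4, rather than 0.5.

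**6. Why 61% is an upper figure on the stated inputs.** It applies ρ = 0.5 to the baseline-adjusted values. If 0.5 is instead the correlation between single readings in different phases, adjustment for each phase's own baseline removes most of it. The slope is 0.6/0.7, so the residual covariance is 0.5 × (1 − 0.857)² = 0.010. The residual correlation is then 0.010/0.186, about 0.05, and power falls to about 37%.

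**7. The measurement count.** Home monitoring gives 3 readings × 3 times × 6 days = 54 per time-point, and the clinic gives 3 per visit. Neither is four.

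**The case against.** The strongest reply is that the trial measures far more than four values per time-point. With the same formula and equal correlation of 0.6 throughout, eight baseline and eight follow-up measures would give about 87% power with 31 completers, nine and nine about 91%, and 18 and 18 (one value per session) over 99%. This stands to the extent that the documents do not fix the real trial's power at 61%. It does not rescue the paragraph. The article states four measures, and the formula treats readings a minute apart as no more alike than readings eight weeks apart, which the article does not claim and which would be optimistic.

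A second reply is that 40 are recruited. Even if all 40 completed, ANCOVA 4/4 gives about 72%.

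Two stronger readings are tempting. One is that power is only 16% (a single reading with SD 14) or 21% (the mean of four readings). Those figures leave out inputs that section 2.7 states: ANCOVA in both cases, and the four measures in the first. They are not the protocol's own case. The other is that the trial would probably miss a true 2.5 mmHg effect. At 61% it would more likely detect it than not, and the actual power is unknown until the home schedule is modelled.

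**Conclusion.** Wrong as written. On the stated inputs, the most favourable reading needs about 123 per group (about 245 in total) in a parallel design and about 62 crossover completers, twice the stated 31. With 31 completers, power for 2.5 mmHg is at most about 61%, and about 38% with a single baseline measure; 90% power is reached only for about 3.6 mmHg.

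The closeness of 123 per group to the stated total of 124 suggests that a per-group figure was taken as the total and halved. That is an inference and cannot be proved from the article; the mismatch itself does not depend on it.

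These figures rest on the article's SD and correlations, equal correlation among the four measures and across baseline and follow-up, and a two-sided 5% test. They show that the calculation on the page fails. They do not show what power the trial will have with the home-monitoring average as its outcome.

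**What to change.** Rewrite the sample-size paragraph of section 2.7, with enrolment unchanged.

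1. Recompute from the SD of the within-person diet difference in mean home systolic pressure under the schedule in section 2.5.1. State separately the correlations assumed within a session, between days, between baseline and follow-up, and between phases.
2. Replace the claim of at least 90% power with the resulting power for 2.5 mmHg and the difference detectable with 90% power. If the four-measure inputs are kept, give about 61% and about 3.6 mmHg, labelled as the best case under those inputs.
3. Replace the four measures per visit with the actual home-monitoring average, and correct (1 − ρ)/2 to 0.25, that is, a division by 4.
4. State that the primary result will be interpreted by its confidence interval against 2.5 mmHg, so that a non-significant result is not taken to exclude that difference unless the interval does.

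The cost is a redrafted paragraph and probably a less favourable stated power. No participants or visits are added.

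### The crossover saving is taken on a parallel-group size already reduced by ANCOVA, so 31 completers do not have the stated 90% power for 2.5 mmHg

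*Protocol article*

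**What the plan says.** All of this is in section 2.7 (Power Calculation and Statistical Analyses) of the protocol article.

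- The target is a "clinically relevant difference of 2.5 mm Hg in the primary outcome measure of systolic home blood pressure", and "with at least 90% power, a sample size of 31 volunteers is required".
- The stated inputs are a "within-group standard deviation (SD) of 14 mmHg", "a within-subject correlation between the 4 blood pressure measures at each visit of" 0.6, and "a between-phase within-subject correlation of" 0.5.
- The text then says that ρ "and the cross-over design reduces the number of required participants by a factor of" (1 − ρ)/2, printed as equal to 4. The starting point is about 124 in total (62 per group) "for a parallel group design using ANCOVA", and the result is 31 in total.
- Nine further volunteers are added for withdrawals, which gives 40.
- The significance level is set once for the whole analysis, at 0.05: "All tests will be 2-tailed and".

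The section does not give the correlation between baseline and end-of-phase values, and it does not say whether ρ is raw or baseline-adjusted.

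**The concern.** ANCOVA on baseline and the crossover save participants for the same reason: each removes variation between people that is stable over time. The factor (1 − ρ)/2 is the full saving of a crossover over a parallel design in which none of that variation has been removed. Applied to an ANCOVA size, it removes again what the baseline has already taken out.

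This is the only power justification for the primary outcome. If the saving is overstated, the trial has less power for 2.5 mmHg than readers are told, and a null result would be read as stronger evidence of no effect than it is.

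**Working it through.** **Inputs.** From section 2.7: Δ = 2.5 mmHg, power 90%, two-sided 5%, SD 14, r = 0.6, ρ = 0.5, parallel total 124. Write z = 1.960 + 1.282 = 3.242, so z² = 10.507. All sizes below are completers, to be compared with 31 and not with 40.

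**The plan's figure.** (1 − 0.5)/2 = 0.25 and 124 × 0.25 = 31. The last step reproduces. The printed 4 is the reciprocal of 0.25 and has no numerical effect.

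**Where the factor comes from.** An unadjusted parallel design needs 4σ²z²/Δ² in total. An unadjusted crossover needs 2σ²(1 − ρ)z²/Δ². The ratio is (1 − ρ)/2. If the parallel design is baseline-adjusted, there are two consistent ways to obtain the ratio:

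- *Own-baseline adjustment in each phase:* (1 − ρₐ)/2, where ρₐ is the between-phase correlation of the baseline-adjusted values.
- *End-of-phase difference adjusted for baseline difference:* D/(4V), where V is the ANCOVA residual variance and D the residual variance of the difference.

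In units of SD², let v be the variance of a phase value, w the baseline-to-end covariance within a phase, and c the covariance of any two values from different phases. Then V = v − w²/v, ρₐ = c(1 − w/v)²/V and D = 2(v − c) − [2(w − c)]²/[2(v − c)].

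| Assumed structure | v, w, c | V | ρₐ | Own-baseline n | D | Difference-on-difference n |
|---|---|---|---|---|---|---|
| One baseline, one end value, w = 0.5 | 1, 0.5, 0.5 | 0.75 | 0.167 | 124 × 0.417 = 51.7 | 1.00 | 124 × 0.333 = 41.3 |
| One baseline, one end value, w = 0.6 | 1, 0.6, 0.5 | 0.64 | 0.125 | 124 × 0.4375 = 54.3 | 0.96 | 124 × 0.375 = 46.5 |
| 4 + 4 readings, r = 0.6 | 0.7, 0.6, 0.5 | 0.186 | 0.055 | 124 × 0.473 = 58.6 | 0.300 | 124 × 0.404 = 50.1 |
| 4 + 4 readings, ρ applied to means | 0.7, 0.6, 0.35 | 0.186 | 0.038 | 124 × 0.481 = 59.6 | 0.343 | 124 × 0.462 = 57.2 |

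The range is about 41 to 60. No row returns 31.

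**Power and detectable difference at 31, taking 124 as given.** If n₀ completers give 90% power by the normal formula, power at 31 from the t distribution with 29 degrees of freedom is about 77% for n₀ = 41.3 and about 62% for n₀ = 59.6. The normal formula gives 80% and 64 to 65%. The detectable difference at 90% power is 2.5 × √(41.3/31) = 2.9 to 2.5 × √(60/31) = 3.5 mmHg (normal formula).

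**Does 124 follow from the stated inputs?** The ANCOVA variance factor for 4 + 4 readings at r = 0.6 is (1 + 3 × 0.6)/4 − 4 × 0.36/(1 + 3 × 0.6) = 0.700 − 0.514 = 0.186.

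- SD 14: 2 × 196 × 10.507/6.25 = 659.0 per group unadjusted; × 0.1857 = 122.4 per group, 244.8 in total.
- SD 10: 2 × 100 × 10.507/6.25 = 336.2 per group unadjusted; × 0.1857 = 62.4 per group, 124.9 in total.

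So 62 per group fits r = 0.6 with 4 + 4 readings only if the SD is about 10. At the stated SD of 14, the two 4 + 4 rows give 0.300 × 196 × 10.507/6.25 = 98.9 at the low end and 2 × 0.1857 × (1 − 0.038) × 196 × 10.507/6.25 ≈ 118 at the high end. Power at 31 is then about 42% down to 36% (t distribution).

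**The case against.** The strongest defence is that ρ = 0.5 might be the correlation of baseline-adjusted values. Then nothing is counted twice and 124 × 0.25 = 31 is coherent. The article does not rule this out in words, and the source cited for the factor is not at hand. But it describes ρ only as a between-phase within-subject correlation. In the structures above the adjusted correlation is 0.04 to 0.17, and with 4 + 4 readings it stays at 0.066 even if c is raised to 0.60. The defence is a reason to define ρ; it does not support the 90%.

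Three stronger readings are tempting, and the document does not carry them.

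- *That 31 should be 59.* That comes from own-baseline adjustment with 4 + 4 readings. Adjusting the end-of-phase difference for the baseline difference gives about 50 under the same model, and a single baseline gives 41 to 54. The article does not say which applies.
- *That ANCOVA has already removed nearly all stable between-person variance.* This holds only under the 4 + 4 model. A single baseline correlated at 0.5 to 0.6 removes 25 to 36% of the outcome variance.
- *That the calculation used an SD of 10.* This is back-solved; the article states 14.

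It is also fair to say that the printed 4 is harmless, and that the mismatch between 124 and an SD of 14 is a separate problem. Correcting the factor alone would leave the sample-size statement wrong.

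**Conclusion.** The point holds. With ρ read as described, the two-step reduction counts the within-person correlation twice, and 31 completers do not give 90% power for 2.5 mmHg. The direction is firm; the size depends on assumptions.

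- *Taking 124 as given:* about 41 to 60 completers needed, power at 31 about 62 to 77%, detectable difference about 2.9 to 3.5 mmHg.
- *At the stated SD of 14 with 4 + 4 readings:* about 99 to 118 completers needed and power at 31 about 36 to 42%.

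These figures assume that the crossover analysis uses the phase baselines, that r = 0.6 also serves as the baseline-to-end correlation where 4 + 4 readings are assumed, and that cross-phase covariances are equal. Leaving the baselines out does not rescue 31. With single readings it gives 124/0.75 × 0.25 = 41 or 124/0.64 × 0.25 = 48, and under the 4 + 4 model it needs more than the range above.

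**What to change.** Replace the two-step reduction in section 2.7 with one crossover calculation:

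1. Base it on the variance of the within-person difference in end-of-phase home systolic pressure, adjusted for the difference in phase baselines if that term will be in the model.
2. State the SD and what it refers to, the number of readings averaged, the baseline-to-end correlation, and whether ρ is raw or baseline-adjusted.
3. Reconcile the 124 with the stated SD of 14.
4. Correct the printed value of (1 − ρ)/2 from 4 to 0.25.
5. Restate the power for 2.5 mmHg, or the difference detectable with 90% power, at 31 completers.

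The cost is a recalculation and a few sentences. Correcting the statement does not require a change in enrolment; the downside is a less favourable stated power.

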## Abstract

The Mediterranean diet has demonstrated efficacy for improving cardiovascular and cognitive health. However, a traditional Mediterranean diet delivers fewer serves of dairy and less dietary calcium than is currently recommended in Australia, which may limit long-term sustainability. The present study aims to evaluate whether a Mediterranean diet with adequate dairy and calcium can improve cardiovascular and cognitive function in an at-risk population, and thereby reduce risk of cardiovascular disease (CVD) and cognitive decline. A randomised, controlled, parallel, crossover design trial will compare a Mediterranean diet supplemented with dairy foods against a low-fat control diet. Forty participants with systolic blood pressure above 120 mmHg and at least two other risk factors of CVD will undertake each dietary intervention for eight weeks, with an eight-week washout period between interventions. Systolic blood pressure will be the primary measure of interest. Secondary outcomes will include measures of cardiometabolic health, dietary compliance, cognitive function, assessed using the Cambridge Neuropsychological Test Automated Battery (CANTAB), psychological well-being and dementia risk. This research will provide empirical evidence as to whether the Mediterranean diet can be modified to provide recommended dairy and calcium intakes while continuing to deliver positive effects for cardiovascular and cognitive health. The findings will hold relevance for the field of preventative healthcare and may contribute to revisions of national dietary guidelines.

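### Nine extra volunteers do not cover 30% withdrawal: 40 recruits leave 28 completers, not the 31 required

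*Protocol article*

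**What the plan says.** Section 2.7 of the protocol article (Power Calculation and Statistical Analyses) gives the primary-outcome requirement as "a sample size of 31 volunteers is required". The target is a difference of 2.5 mmHg "in the primary outcome measure of systolic home blood pressure with at least 90% power". The 31 comes from a parallel-group total of about 124, divided by four for the crossover design. The paragraph ends with the allowance for losses: "To account for a withdrawal rate of 30%, an additional 9 volunteers will be recruited". The Abstract gives the resulting total: "Forty participants with systolic blood pressure above 120 mmHg".

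The article does not provide for replacing people who withdraw. The Diet Adherence part of section 2.5.2 adds a further way to lose participants: those who cannot raise their adherence above 75% by the following fortnight are removed from the study.

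**The concern.** A withdrawal rate is a proportion of the people who enter the trial. To end with 31 after losing 30%, the 31 must be divided by 0.70. Adding 30% of 31 to 31 gives too few, because the loss then falls on the larger, recruited number.

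At the withdrawal rate the protocol itself expects, the trial would therefore finish below the number to which it attaches its 90% power. The text also tells the reader that the design is protected against 30% withdrawal, and it is not.

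**Working it through.** **Inputs.** All are from section 2.7 unless noted: required number 31; withdrawal 30%; additional volunteers 9; total recruited 31 + 9 = 40 (confirmed in the Abstract); power at least 90%; two-sided tests at 0.05.

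**1. Reproduce the plan's figures.**
- Crossover requirement: 124 × (1 − 0.5)/2 = 124 × 0.25 = 31.
- Allowance: 31 × 0.30 = 9.3, rounded down to 9, so 31 × 1.30 = 40.3, or 40.

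The stated 40 is reproduced by applying 30% to the number needed. The usual inflation, n/(1 − d), does not give 40.

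**2. Apply the withdrawal rate to those recruited.**
- Completers from 40: 40 × 0.70 = 28, which is 3 (10%) fewer than 31.
- Recruits needed for 31 completers: 31/0.70 = 44.3, so 45 (14 extra, not 9). Check: 45 × 0.70 = 31.5, whereas 44 × 0.70 = 30.8.
- Withdrawal that 40 recruits can absorb: 9/40 = 22.5%.

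**3. Effect on power, taking the 90% at n = 31 as given** (normal approximation).
- At n = 31 the standardised effect is 1.960 + 1.282 = 3.2415.
- At n = 28 it is 3.2415 × √(28/31) = 3.0807.
- Power = Φ(3.0807 − 1.960) = Φ(1.121) = 0.869.
- Difference detectable with 90% power at n = 28: 2.5 × √(31/28) = 2.63 mmHg.

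**4. Chance of reaching 31 completers**, with each participant withdrawing independently with probability 0.30 (binomial).
- From 40 recruits: P(at least 31) = 0.196.
- From 45 recruits: P(at least 31) = 0.635.

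**5. If the 31 is itself too small** (a side calculation on an assumed reading). Section 2.7 gives an SD of 14 mmHg and a correlation of 0.6 between four blood pressure measures. Assume ANCOVA with four baseline and four follow-up measures.
- Variance factor: (1 + 3 × 0.6)/4 − 4 × 0.6²/(1 + 3 × 0.6) = 0.700 − 0.514 = 0.186.
- Number per group: 2 × 14² × 0.186 × 3.2415²/2.5² ≈ 122, against the 62 stated.
- Total of about 245, divided by four for the crossover: about 61.
- Power by paired t (noncentral t): about 61% with 31 completers and 56% with 28. The normal approximation used in step 3 gives about 64% and 59%.

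This step shows only that a larger true requirement would widen the shortfall. The finding does not depend on it.

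**The case against.** The strongest reply is that the loss is small. About 87% power is still above the 80% that section 2.7 accepts for the cognitive outcomes, and 28 completers exceed the 22 stated for them. That is correct, and it confines the effect to the primary outcome.

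A second reply is that section 2.7 specifies a linear mixed-effects analysis, which can use data from people who leave after Phase 1, so counting only completers overstates the loss. This holds in part. The 31, however, depends on the crossover reduction, which comes from comparing the two diets within the same person, and someone seen in one phase only adds little to that comparison. The protocol also treats withdrawals as lost by adding volunteers to cover them.

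A third reply is that 30% may have been meant loosely, as a margin on top of the target (9/31 = 29%). The text calls it a withdrawal rate, and nothing redefines the term.

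Finally, the 61% and 56% figures rest on an assumed analysis structure and on a different approximation from the 87%. That objection is fair. They belong with the separate question of the base sample size and should not be added to this one as further harm.

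**Conclusion.** The allowance is wrong as written. Required number, withdrawal rate and number of extra volunteers are all stated, and they are inconsistent: 40 recruits with 30% withdrawal give 28 completers, not 31. The size is modest: 10% fewer completers than required and about three points of primary-outcome power (90% to 87%). The trial would also be more likely than not to miss its own target.

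The 28, 45 and 22.5% need only the protocol's own figures and the ordinary meaning of a withdrawal rate. The 87% further assumes that 31 gives exactly 90%, that those who withdraw contribute nothing, and a normal approximation. The 20% assumes independent withdrawals.

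**What to change.** Keep 40 recruits and correct the sentence in section 2.7, for example: nine additional volunteers allow for 22.5% withdrawal; at 30% withdrawal 28 participants would complete. Then give the power at 28 completers (about 87% if 31 gives 90%) or the detectable difference (2.63 mmHg at 90% power). If the base figure of 31 is recalculated, recompute these from the new base in the same revision.

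The cost is one sentence and a slightly less favourable stated figure; design, randomisation and conduct do not change. If the sponsor prefers to keep both the 31 and the 30%, the alternative is to recruit 45, five more than planned.
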